With regard to *Aedes*-transmitted infections, DENV is most common in Cambodia and is highly endemic with year-round transmission, peaking from July to November when rainfall is at its highest. Transmission is highly focal but is found in both rural and urban areas in Cambodia [23, 24]. The National Dengue Control Programme (NDCP) has a pediatric hospital-based syndromic surveillance system across the country. At five sentinel sites, clinically suspected cases are sent to Pasteur Institute to confirm DENV infection *via* RT-PCR detection of the virus [20]. Epidemiological studies otherwise rely upon reports of clinically diagnosed dengue-like cases (occasionally confirmed by SD Bioline Dengue Duo rapid tests when available) from hospitalized children under 16 years of age, with little assessment or data in older adults who are less likely to seek care. In Cambodia, average DENV incidence appears to be highest in those under 7 years of age (approximately 41 cases per 1000 person-seasons in one active community-based surveillance study from 2006 to 2008) [24]. Given its reliance on a clinical reporting system, national DENV incidence data likely underestimates true DENV incidence in Cambodia by 3 to 27-fold, per capture-recapture analyses [25]. Among other arboviruses, CHIKV outbreaks are occasionally documented in Cambodia, e.g. one village in Kampong Speu Province experienced a 44% attack rate in 2012 [26]. ZIKV transmission is uncharacterized and may sporadically occur in Cambodia [20].

Considering the vector abundance of *Aedes* mosquitos and the presence of multiple *Aedes*-transmitted viruses in Cambodia, we chose to establish a prospective pediatric cohort using local pagodas (religious temples) for community recruitment and follow-up. This study protocol aims to define the seroprevalence of antibodies to both DENV and *Aedes aegypti* salivary gland homogenate (SGH), describe the epidemiology of symptomatic *Aedes*-transmitted infection in children in this community, characterize the demographic and entomological factors that contribute to DENV infection, and establish the magnitude of human antibody response to *Ae. aegypti* saliva. These data will establish the groundwork on which to better understand the roles of vector-borne determinants of arboviral infection.

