Describe epidemiology of symptomatic *Aedes*-transmitted infections in a Cambodian pediatric population	Positive RT-PCR result for diagnosis of dengue, chikungunya, and Zika viruses (or IgM capture ELISAs for dengue as needed)	Dengue is the predominant flavivirus, but other circulating arboviruses complicate the serologic diagnosis of prior immunity and it will be important to characterize this burden given the ease and little cost added to run the multiplex RT-PCR compared to a DENV RT-PCR alone
Establish and characterize spatial relationships between population abundance of *Ae. aegypti* (through entomological indicators), magnitude of human antibody response to *Ae. aegypti* mosquito saliva, and disease development	Geographical information system with all data components (mosquito catch sites, houses, schools) referenced by latitude and longitude in addition to a series of map layers (point maps, smoothed maps) to evaluate relationships between IgG intensity of human antibody response (ΔOD per ELISA) to *Ae. aegypti* salivary homogenate, entomological indices (e.g. House index defined as larvae present per 100 houses surveyed), and disease development	These data and analyses will allow for detailed spatio-temporal analysis of the data at individual, house and community levels. Similar published methods (except different entomological indices) were used for assessment of *Anopheles* salivary protein exposure at the Thai-Burma border for risk of malaria transmission [53]
Characterize temporal dynamics of human antibody reactivity to *Ae. aegypti* salivary gland homogenate	Seroconversion to *Ae. aegypti* salivary homogenate in relationship to season (wet *versus* dry) and collected time-dependent variables defined as mean and maximum rainfall, temperature and humidity	The natural time course of salivary protein exposure, particularly in confirmed arboviral disease settings, has not been well characterized. Retrospective repeat analyses of non-diseased samples have suggested that salivary IgG antibodies may last 30–40 days or possibly up to 4 months [18]. Seasonal variation and climate factors are implicated in both disease transmission and vector abundance [54, 55]. Quantifying vector-host interaction at the individual level in the context of more global factors is necessary to further understanding saliva immunity, disease transmission, and outbreak model prediction

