Demographics	×									
Baseline medical history questionnaire	×									
Baseline physical exam	×									
Interval exam and questionnaire		×	×	×	×	×	×			
Concomitant medication review	×	×	×	×	×	×	×	×	×	×
Sick visit exam (with height and weight) and questionnaire								×		
Convalescent exam and questionnaire									×	×
Height and weight	×						×	×		
Vital signs	×	×	×	×	×	×	×	×	×	×
Dengue rapid diagnostic test (RDT)								×		
RT-PCR multiplex for acute arboviral diagnosis								× (if RDT+)		
Sera collection for ELISAs	×	×	×	×	×	×	×	× (if RDT+)	×	
Hemoglobin		×								
Alpha-thalassemia screening		×								
Peripheral blood mononuclear cells	×						×	× (if RDT+)		×
Complete case report forms	×	×	×	×	×	×	×	×	×	×

*Note*: Dry seasons visits take place every March whereas wet season visit take place every August

To reduce bias from loss to follow-up, the study team enrolls volunteers who are located within 5.5 km of the district hospital, will do follow-up sampling in the community, and will provide incentives commensurate with the previous studies approved by the Cambodian ethics committee.

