Sick febrile visits may occur at any point during the three years. Upon enrollment, participants are given a thermometer to monitor their temperatures at home, call their Community Engagement liaison if they have a fever, and go to the Pediatrics ward at the referral hospital and present their study identification card to undergo vital signs, a dengue-specific sick questionnaire, targeted exam, and rapid diagnostic dengue test. Per Cambodian National Dengue Treatment Guidelines, all children with symptomatic dengue infection are hospitalized. If a patient is found to screen positive for dengue using the SD Bioline Dengue Duo kit, the participant undergoes the following: (i) Day 0 collection for RT-PCR confirmation of arboviral diagnosis, sera for *Ae. aegypti* SGH ELISA and dengue IgM dengue IgM/IgG ELISA, and PBMCs; (ii) Day 7 collection of 5 ml in SST for paired sera between acute and convalescent samples to detect IgM seroconversion or 4-fold increase in total anti-DENV antibodies as measured by ELISA; and (iii) Day 28 collection for 5 ml in SST for sera and 8 ml in heparinized tube for PBMCs for cellular assays. Complete blood counts are already performed as part of the hospitalization per national treatment guidelines, and this information is captured in the patient’s clinical research form (CRF). If the result of the dengue rapid test is negative, the physician will manage the participant as a non-dengue case and advise them accordingly. If the doctor still strongly suspects dengue despite negative rapid testing, or he/she suspects CHIKV or ZIKV infection, the study physician may request collection of 1 ml of whole blood in an EDTA tube to undergo Fast Track Diagnostics® RT-PCR multiplex testing for the viruses in the central CNM-NIH laboratory in Phnom Penh. Of note, no additional phlebotomy for research purposes at sick visits will be performed if a child just underwent venipuncture at a scheduled visit within the preceding 14 days.

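### The 14-day limit on research blood draws conflicts with the Day 0 sampling in the design text and Table 2, and costs about 9% of peak-season cases their RT-PCR confirmation

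*Protocol article*

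**What the plan says.** For a child who screens positive on the rapid test, Clinical and laboratory procedures lists "Day 0 collection for RT-PCR confirmation of arboviral diagnosis", with serum for the salivary gland homogenate (SGH) and dengue ELISAs and with PBMCs. A Day 7 serum (to be paired with the acute one) and a Day 28 collection follow. The same paragraph ends with the limit: "no additional phlebotomy for research purposes at sick visits will be performed if a child just underwent venipuncture at a scheduled visit" in the previous 14 days. It makes no exception for rapid-test-positive children and names no replacement sample.

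Two other places describe the same sampling without the limit. Study design and objectives has RT-PCR performed for febrile cases with a positive rapid test or high clinical suspicion. Table 2 marks RT-PCR, serum and PBMCs at the febrile sick visit as due if the rapid test is positive.

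On timing, Background describes dengue transmission as year-round, "peaking from July to November when rainfall is at its highest", and the note to Table 2 says that the "wet season visit take place every August". On routine blood, the article says: "Complete blood counts are already performed as part of the hospitalization per national treatment guidelines".

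**The concern.** The Day 0 draws are research draws. Community engagement states that the hospital is not one of the five RT-PCR sentinel sites and that samples travel to the central laboratory. The complete blood count (CBC) is the only blood described as routine care. The limit therefore removes all three acute samples from a rapid-test-positive child seen within 14 days of a scheduled visit.

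The wet-season visit is placed in the transmission peak, so the gap recurs each year when cases are expected. Two endpoints in Table 1 depend on the lost samples:

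- The secondary endpoint is a positive RT-PCR for dengue, chikungunya or Zika, with IgM capture ELISA as a fallback for dengue only.
- The exploratory cellular endpoint uses the acute time point in RT-PCR-confirmed infection.

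The article does not say how a child who could not be sampled is to be classified.

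**Working it through.** The plan gives no figure for this loss, so there is none to reproduce. The check has a textual part and an arithmetical part.

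**Text.** Read literally, the limit overrides the Day 0 list that precedes it. The design text and Table 2 do not carry it, so a site following Table 2 would draw blood that the procedures section bars. Table 2 has separate columns for the febrile sick visit and the two convalescent visits. Because the limit names sick visits, the Day 7 and Day 28 draws appear to survive. The text does not say whether the limit covers the 1 ml EDTA draw that a study physician may request for a rapid-test-negative suspect. That draw is the stated route to RT-PCR for suspected chikungunya or Zika.

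**Is the window inside the peak?** The visit columns of Table 2 carry ± 28 days. Applied at its widest to August, this runs from 4 July to 28 September, and the 14 days after the last date end on 12 October. All of it lies within July-November.

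**Inputs**
- Window: 14 days (Clinical and laboratory procedures).
- Peak: July to November, 31 + 31 + 30 + 31 + 30 = 153 days (Background).
- Incidence: 13.7 to 58 per 1000 person-seasons, from a neighbouring province (Sample size calculation).
- Children: 701 after dropout, 771 enrolled (Sample size calculation).
- Assumptions: cases fall evenly over July-November, and the neighbouring-province incidence applies here.

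**Share of peak-season cases in one window**
14/153 = 0.0915, about 9%.

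**Cases per season with 701 children**
- Low: 701 × 13.7/1000 = 9.6 cases; 9.6 × 0.0915 = 0.9 without Day 0 samples.
- High: 701 × 58/1000 = 40.7 cases; 40.7 × 0.0915 = 3.7 without Day 0 samples.

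**Over the study**
- Two wet-season windows: 1.8 to 7.4 cases.
- Three windows: 2.6 to 11.2 cases.

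The range of two to three is needed because the third wet-season visit is the last scheduled one, and the article does not say whether sick visits continue after it. With all 771 children retained, the loss is 1.0 to 4.1 per season.

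**Recency of the saliva serum.** Table 1 reports that "salivary IgG antibodies may last 30–40 days or possibly up to 4 months". With even onset after the August visit, the share of cases with a scheduled serum still within that persistence that fall in the 14-day window is 14/40 = 35% to 14/30 = 47%. It is 14/120 = 12% if persistence is four months.

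**The case against.** The limit is evidently a deliberate cap on blood taken from young children, introduced as an exception, and a summary table may simply omit it. That is fair as an explanation, and nothing here asks for the cap to change. It does not remove the need to make the places agree, or to say what happens to the affected cases.

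Much of the rest of the defence stands:

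- Day 7 serum appears to survive. Together with the serum taken 0 to 14 days before illness it can show dengue IgM seroconversion, which the secondary endpoint allows. Later semi-annual ELISA and PRNT can also detect dengue infection.
- The exploratory saliva-disease analysis takes exposure from baseline and follow-up visits, and the Discussion says that its endpoints include inapparent as well as symptomatic dengue.
- The Discussion already concedes that the study is not powered for acute dengue incidence.

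A reader might infer that the rule discards the cases with the best pre-illness saliva measurement. The documents do not support this. The saliva serum is drawn at the scheduled visit and kept. Children who fall ill on days 15 to 40 also have a recent serum and keep their Day 0 draw. No incubation period is given, so some sera taken just before illness may post-date the infecting bite. "Most recent" is as far as the text goes.

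**Conclusion.** The point holds as an internal inconsistency with a small, recurring loss. About 9% of peak-season cases, roughly 0.9 to 3.7 per season with 701 children, would lack Day 0 RT-PCR, acute serum and acute PBMCs. That is about 2 to 7 cases over two windows, or 3 to 11 over three. The figures rest on even onset over the peak and on the neighbouring-province incidence. They fall if part of the incidence lies outside July-November and rise if cases cluster just after the visit. March visits create further windows, outside the peak, that are not counted.

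The loss affects the secondary RT-PCR endpoint, most plainly for chikungunya and Zika, which have no IgM fallback, and the exploratory acute cellular endpoint. Both primary endpoints rest on scheduled sera and are unaffected.

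A reader might also infer a biased saliva-disease association. That is not shown: the window is set by the visit date and applies alike to saliva-positive and saliva-negative children. Nor is it shown that dengue cases in the window go undetected. This is worth correcting because the correction is cheap, not because the study's main results are at risk.

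**What to change.** Reconcile Clinical and laboratory procedures with Study design and objectives and Table 2, for example by a footnote to the table that states the exception, and say whether it covers the 1 ml EDTA draw. Leave the limit on blood draws unchanged and add, for children inside the 14-day window:

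1. The serum from the scheduled visit is the pre-illness member of the pair with Day 7, for the dengue IgM/IgG and SGH ELISAs.
2. The multiplex RT-PCR is run on residual blood from the clinical CBC where tube type and volume allow.
3. These cases are flagged and classified by the paired-serum result, not counted as non-cases.

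The cost is a few sentences and an agreement with the hospital laboratory to keep the residual tube, with no extra draw or visit. The article does not state the CBC tube type or whether residual blood is kept, so RT-PCR will sometimes not be possible. A dengue serum pair cannot then settle a suspected chikungunya or Zika case. Acute PBMCs are not recovered in any event.

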### Data collection, monitoring, and storage of research samples

Upon enrollment in the protocol, all subjects will be assigned a unique identifying combination code of seven numbers (e.g. 100-0001). The identifier will serve to link this identifying code with subject name. CRFs, databases, and biological samples including DNA will be coded with unique identifying numbers and will not contain subject names. Study personnel involved in data acquisition, entry, and analysis will therefore not have access to names, assuring the privacy and confidentiality of subjects.

REDCap (Research Electronic Data Capture) serves as the core data collection component of the data management system hosted at NIAID. REDCap is a secure, web-based application designed to support data capture for research studies, providing: (i) an intuitive interface for validated data entry; (ii) audit trails for tracking data manipulation and export procedures; (iii) automated export procedures for seamless data downloads to common statistical packages; and (iv) procedures for importing data from external sources [32]. Standard CRFs containing clinical and laboratory data will be completed on iPads using the REDCap that will be locked with a code and uploaded to password-protected servers. Relevant subject data will be entered into a hybrid system (REDCap plus Datafax©). Electronically captured data will be checked by study investigators and verified by a data manager. All electronic data will be stored on a secure server.

Following written standard operating procedures (SOPs), external study monitors will verify that the clinical trial is conducted, data are generated, and biological specimens are collected, documented (recorded), and reported in compliance with the protocol, good clinical practices, and applicable regulatory requirements.

The PI will retain all study records for at least 5 years in compliance with institutional, institutional review board (IRB), state, and federal medical records retention requirements, whichever is longest. Data captured electronically *via* tablets will be backed up nightly to the site’s central server and transmitted on a weekly basis. All data will be archived at the end of the study and retained for a period of time consistent with IRB requirements.

All human biological samples will be received, processed, aliquoted, and stored at the central CNM laboratory in Phnom Penh according to standard laboratory procedures.

A geographical information system (GIS) was set up at the beginning of the study, following GPS training of survey and community engagement team members. All data are geographically referenced, with geographic coordinates (latitude, longitude and elevation) collected for all recruitment locations (participant pagodas), mosquito catch sites, and participant houses.

### Statistical analysis

The primary endpoints will be defined as:(i)Seropositivity to DENV1-4 per indirect IgG ELISA (with plaque reduction neutralization assays performed as necessary to confirm inapparent dengue infections)(ii)Seropositivity to *Ae. aegypti* salivary gland homogenate

Seroprevalence to each dengue serotype will be presented as a proportion for each timepoint. Unadjusted and adjusted logistic regression models will be performed evaluating the relationship between time and seroprevalence, with adjustments for age, year or season of collection, and socio-economic conditions (e.g. type of housing). Further, the seroconversion rate and change in the immune status will be determined by participants and separated by age group during the study period. Quasi-Poisson regression models will be fit to evaluate the relationship of age, year, socio-economic conditions (e.g. type of housing) to the primary endpoints of dengue infection or *Ae. aegypti* salivary gland homogenate seropositivity and to estimate prevalence ratios.

Because seroconversion to *Ae. aegypti* salivary gland homogenate is measured repeatedly on subjects over three years during wet and dry season, a single subject may be negative for seroconversion at one time, and positive at a later time. This will allow us to perform our secondary objective to evaluate the kinetics of the antibody response. Given these changing values, seroprevalence to *Ae. aegypti* salivary gland homogenate will be presented as proportion representing point prevalence for each season in each year of the study.

We will perform regression models (logistic for dichotomy predictors, quasi-Poisson models for incidence rates, linear models or mixed models for continuous predictors), to investigate the effect of environmental and socio-demographic conditions on the prevalence of *Aedes* salivary protein seroconversion (e.g. age, type of housing, number of domestic water containers) and season-specific data such a humidity, temperature and rainfall. All data will be geographically referenced. To evaluate spatial or temporal aggregation of salivary gland seroconversion, space-time scan statistics will be used. Exploratory spatial analyses will look for statistical clustering of disease, of IgG response and of mosquito abundance using both global and local indicators of spatial autocorrelation [33]. Smoothed heat maps will be created using QGIS software (https://www.qgis.org/en/site/). Spatial data will then be used to estimate risk factors for strongly positive antibody response to *Ae. aegypti* saliva and to risk of disease using generalized linear regression or generalized additive models (quasi-Poisson and logistic regression models), where appropriate.

The difference between groups in continuous secondary/exploratory outcomes will be tested by nonparametric Wilcoxon rank sum test, or if inferences on differences in means are desired, using a 2-sample t-test [34]. To test for differences among more than two groups, either a Kruskal-Wallis rank test (for nonparametric inferences) or a one-way ANOVA (for inferences on the means) will be used to test for overall differences. An appropriate data transformation (e.g. log_10_-transformation) may be applied to make inferences on ratios of geometrics means or to better satisfy assumptions of symmetry and homoscedasticity (similar variance).

Exploratory analyses for the relationship of *Ae. aegypti* saliva seroconversion with disease development will model the rate of incidence of composite *Aedes*-transmitted arboviral disease (as defined above) using a quasi-Poisson model. The primary interest will be in the relative risk (RR) of infection comparing at risk subjects with seroconversion to *Ae. aegypti* salivary protein to those without seroconversion at that time. Exposed will be defined as those with seroconversion to specific *Ae. aegypti* salivary protein while unexposed will be those without reactivity at baseline and each follow-up time point. For this analysis, seroconversion will be defined as a binary variable (present/absent) based on the level of antibody to *Ae. aegypti* salivary gland homogenate (positivity is generally considered two standard deviations above the mean optical density value for negative controls as determined by an ELISA assay with further adjustment as needed to account for cross-reactivity to *Anopheles* or *Culex* saliva).

To compare the rates in secondary/exploratory outcomes for significant differences in arboviral infection between participants with or without evidence of salivary protein exposures or to examine other groups such as alpha thalassemia variants, we will use quasi-Poisson models and central Fisher’s exact tests. As previously stated, secondary and exploratory analyses will evaluate ELISA values as background (negative), low, medium and high quartiles, based on range and as a continuous variable. From the subset of samples with the highest positive values from both primary and secondary analyses, Western blot assays will be used to identify the most immunodominant protein candidates for functional characterization and future studies on epitope identification and characterization. Western blot assays will also be run against *Culex* and *Anopheles* saliva to account for cross-reactive immunogenicity to mosquito saliva in general.

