## Methods/Design

### Study design and objectives

This is a prospective pagoda (community)-based cohort study with the following primary objectives: (i) to determine the seroprevalence of antibodies indicating previous *Aedes*-transmitted DENV infection in children; and (ii) to describe the seropositivity to *Aedes* salivary gland homogenate (Table 1). The study will screen up to 1200 and recruit up to 771 children aged 2–9 years for study enrollment and then follow them longitudinally for three years. The study is being conducted over three years given the high rate of variability in *Aedes*-transmitted disease transmission from year to year. The study is focused on children aged 2–9 years of age as they have the greatest burden of disease in Cambodia and thus offers comparability to other pediatric DENV cohorts [23–25, 27].

**Table 1 Tab1:** Study objectives and endpoints

Objectives	Endpoints	Justification for endpoints
• Primary		
Describe the seroprevalence of dengue infection (both symptomatic and inapparent) in children aged 2–9 years-old in Kampong Speu	Prevalence of symptomatic and inapparent dengue infection (serotypes 1–4) as detected semiannually *via* ELISA (binary outcome present/absent) over a 3-year period in Kampong Speu in children aged 2–9 years-old	Detailed knowledge of dengue seroprevalence and transmission season variability will help establish an epidemiological foundation to prepare for larger future studies such as disease incidence studies or vector interventional trials
Describe the seroprevalence of reactivity to *Ae. aegypti* salivary gland proteins in children aged 2–9 years-old in Kampong Speu	Prevalence of *Ae. aegypti* salivary gland homogenate reactivity as detected by ELISA assay (binary outcome present/absent) during wet and dry seasons over a 3-year period in Kampong Speu in children aged 2–9 years-old	Characterizing the *Ae. aegypti* salivary protein reactivity profile in Cambodians is the first step prior to assessing how *Ae. aegypti* saliva exposure modulates disease in humans
• Secondary		

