### Sample size calculation

There are no published seroprevalence studies exclusively for Cambodian children, but multiple pediatric seroprevalence studies are reported from neighboring Thailand and Malaysia [29–31]. The most recent incidence studies in Cambodia suggest that the most conservative estimate, or the lowest incidence rate, of acute dengue infection in Cambodia as approximately 14 per 1000 person-seasons (range 13.7–58 per 1000 person-seasons in neighboring province to Kampong Speu) [24].

It is difficult to make presumptions regarding the exposed mosquito saliva protein (MSP+) and unexposed mosquito saliva protein (MSP-) populations as the only available retrospective study data from Thailand suggested that seroconversion occurs to major *Ae. aegypti* proteins 0–25% of the time in non-infected hospitalized children *versus* 0–75% in DENV-infected hospitalized children [19]. Therefore, the sample size was primarily determined by the number necessary for DENV seroprevalence. With a sample size of 701 accounting for 10% dropout to yield a total goal enrollment of 771 participants, a simple random sample of a binary response (infected or not) with an exact 95% confidence interval on the true proportion will have an average length of less than or equal to 0.075 regardless of the true rate.

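### Prevalence ratios for the two binary primary endpoints are planned with quasi-Poisson models, whose variance does not fit 0/1 data; a robust variance clustered on child should be stated

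*Protocol article*

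**What the plan says.** Table 1 defines both primary endpoints as yes/no results per child and visit. Dengue seropositivity is a "binary outcome present/absent) over a 3-year period" and saliva reactivity a "binary outcome present/absent) during wet and dry seasons over a 3-year period".

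The Statistical analysis section then plans three things for them:
- proportions, by timepoint for dengue and by season and year for saliva;
- for time trends, "Unadjusted and adjusted logistic regression models will be performed evaluating the relationship between time and seroprevalence";
- for covariates, "Quasi-Poisson regression models will be fit to evaluate the relationship of age, year, socio-economic conditions (e.g. type of housing) to the primary endpoints". That sentence ends with "salivary gland homogenate seropositivity and to estimate prevalence ratios".

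No robust, sandwich or clustered variance is named for the third item. The same section notes that saliva reactivity is "measured repeatedly on subjects over three years during wet and dry season". Table 2 schedules serum at enrolment and at six seasonal visits, so up to seven per child. A later paragraph of the section links quasi-Poisson models with incidence rates, where they fit more naturally.

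**The concern.** A quasi-Poisson model is defined by its variance assumption: variance = phi × mean, with one phi for all observations. A 0/1 outcome with probability p has variance p(1-p), so the factor needed is 1-p, which changes with prevalence. The single estimated phi settles near the average of 1-p over all children. That is right for every group only if all groups have the same prevalence, yet the models exist to estimate how prevalence differs by age, year and socio-economic condition.

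At stake are the standard errors, intervals and p-values of the covariate prevalence ratios for both primary endpoints. The point estimates are not at stake.

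**Working it through.** **The plan's own figure.** The sample size section states "With a sample size of 701 accounting for 10% dropout to yield a total goal enrollment of 771 participants" and that "an exact 95% confidence interval on the true proportion will have an average length of less than or equal to 0.075" whatever the true rate. At n = 701 and p = 0.5 (the worst case) the average exact interval length is 0.0753, which rounds to 0.075, and 701 × 1.10 = 771. The figure reproduces, but it concerns a single proportion and does not bear on prevalence ratios.

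**Inputs.** Four age bands come from the Community engagement section (about 192 each at enrolment). Among 701 evaluable children that is about 175 each. Prevalence by band is not given, so every prevalence below is an assumption.

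**Formulas, one observation per child.**
- phi = average of (1-p) over all children.
- Quasi-Poisson variance of a log prevalence ratio = phi × [1/(n₁p₁) + 1/(n₂p₂)].
- True variance = (1-p₁)/(n₁p₁) + (1-p₂)/(n₂p₂).
- k = quasi-Poisson SE / true SE; coverage = 2Φ(1.96k) - 1.

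**Worked case, 10/25/40/55%.** phi = (0.90 + 0.75 + 0.60 + 0.45)/4 = 0.675.
- Youngest two bands: model variance 0.675 × (1/17.5 + 1/43.75) = 0.0540, SE 0.232. True variance 0.90/17.5 + 0.75/43.75 = 0.0686, SE 0.262. k = 0.887, coverage 91.8%.
- Oldest two bands: model variance 0.675 × (1/70 + 1/96.25) = 0.0167, SE 0.129. True variance 0.60/70 + 0.45/96.25 = 0.0132, SE 0.115. k = 1.121, coverage 97.2%.

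**Range over assumed prevalences.**

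| Four bands | phi | Youngest two: k, coverage | Oldest two: k, coverage |
|---|---|---|---|
| 5/10/15/20% | 0.875 | 0.968, 94.2% | 1.028, 95.6% |
| 10/25/40/55% | 0.675 | 0.887, 91.8% | 1.121, 97.2% |
| 20/40/60/75% | 0.5125 | 0.836, 89.9% | 1.240, 98.5% |
| 30% throughout | 0.700 | 1.000, 95% | 1.000, 95% |

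Simulation with 175 children per band agrees. At 10/25/40/55%, quasi-Poisson coverage was 92.2% and 97.4%, and the robust variance gave 95.4% for both contrasts. In simulations of 20/40/60/75%, quasi-Poisson coverage for the oldest two bands was 98.7-98.8%.

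**Direction depends on both groups.**
- Two equal groups of size n: true minus model variance = (p₁-p₂)²/(2n p₁p₂), never negative, so the interval is never too wide.
- Unequal groups at 20% and 60%: with 600 and 101 children, phi = 0.742 and k = 1.18 (too wide). With 101 and 600, phi = 0.458 and k = 0.77 (too narrow, coverage 86.7%).

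**Pooled rounds.** A year effect cannot be estimated from one round, so the planned model pools visits. Assume seven visits and a within-child correlation of 0.6. For a covariate that is fixed within the child, the variance is inflated by 1 + 6 × 0.6 = 4.6, so an unclustered SE is multiplied by 1/√4.6 = 0.466 relative to the truth.
- Flat prevalence: coverage 2Φ(1.96 × 0.466) - 1 = 64%.
- 10/25/40/55%: k = 0.887 × 0.466 = 0.41 (coverage 58%) for the youngest two bands, and 1.121 × 0.466 = 0.52 (69%) for the oldest two.

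Simulation of the 10/25/40/55% case gave 56-59% against the lowest band and 68% for the oldest two. Clustering the sandwich on child gave 94-96%.

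Contrasts between years within the same children behave differently. There positive correlation partly cancels. For two single visits at similar prevalence the true variance is about 1 - 0.6 = 0.4 of the independence value, so an unclustered interval is too wide.

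**The case against.** The strongest reply has four parts.

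1. **The primary objectives are descriptive.** They are answered by proportions, and the sample size rests on an interval for a proportion. No primary test uses these ratios, and the logistic models already carry the binomial variance. This stands as a limit on importance, although logistic models give odds ratios and do not replace the prevalence ratios.

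2. **The size is assumed and often small.** This stands. Two equal groups at 30% and 40% give k = 0.995. An age-adjusted housing ratio of 1.3 on the 10/25/40/55% pattern gives k = 1.15, 1.08 or 1.02 when 20%, 50% or 80% of children are exposed, which is mildly conservative. A roughly log-linear age trend (10/17/30/52%) gives k = 1.00 for the slope. The article does not say that age will enter in bands. The larger errors need categorical contrasts over a steep gradient.

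3. **A reader might infer a simple rule: too narrow for low-prevalence groups, too wide for high-prevalence ones.** The rule is exact only for each group's own log prevalence with one observation per child. A ratio belongs to a pair of groups, and the 600/101 example is too wide although it includes the low-prevalence group. Once visits are pooled without clustering, the age contrasts that were too wide in one round become too narrow.

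4. **A fuller analysis plan could name a robust variance without contradicting the article.** That is possible. But the article does not merely leave the estimator open: it names a method whose defining variance is wrong for the stated outcome scale.

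**Conclusion.** The point holds in a limited form. The stated method does not match binary endpoints, and its prevalence-ratio intervals are miscalibrated when prevalence differs materially between groups. In one round, under the assumed steep age gradients, coverage runs from about 90% to about 98-99% depending on the contrast. At 5-20% prevalence it stays within about a point of 95%, and with flat prevalence there is no error. In pooled data, unhandled within-child correlation is the larger problem for age and housing contrasts, with coverage of roughly 56-69% at the assumed correlation of 0.6 and the 10/25/40/55% pattern.

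Two stronger readings are not supported. It cannot be said that these intervals necessarily fail to cover 95%, because the article gives no prevalence by group. Nor are the primary results invalid: the seroprevalence proportions and the ratio estimates themselves do not depend on phi. The variance mismatch is certain; its size in this cohort is unknown.

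**What to change.** In the Statistical analysis section, state that prevalence ratios for the two binary endpoints come from a log-link Poisson model with robust (sandwich) variance clustered on child. A log-binomial model with child-clustered variance would serve equally. Keep quasi-Poisson for counts and incidence rates.

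The cost is one sentence. Data, covariates and the ratio being estimated stay the same, and with the Poisson form so do the point estimates. Nothing is lost where prevalence is flat. Some intervals will widen, most clearly those for age and housing in pooled data.
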